### Limitations

Several limitations should be considered. First, due to the nature of the intervention, it will not be possible to blind the participants or the professionals delivering the workshop. This may introduce biases related to the participants’ expectations or to the dynamics of the intervention itself. However, the researcher responsible for data analysis will remain blinded to the participants’ allocation. Group interaction and peer support may also influence the participants’ expectations and self-reported responses.

Second, outcomes will be assessed using self-reported measures, including pain intensity, well-being, mood, perceived usefulness of the techniques, and satisfaction with the workshop. Although these measures are appropriate for the study aims, they may be influenced by recall bias, social desirability, or participants’ expectations regarding the intervention.

Third, between-group comparisons will be limited to the first 4 months, as the participants in the control group will be offered the opportunity to attend the workshop after this period. Therefore, the 7-month assessment will only allow maintenance of effects to be explored within the intervention group.

Fourth, the multicomponent nature of the intervention will limit attribution of the observed effects to specific techniques included in the workshop. The intervention combines therapeutic education, professional input, peer interaction, home-based practice, and digital support. The results should, therefore, be interpreted as reflecting the overall effect of the program, rather than the isolated efficacy or relative contribution of its individual components.

Fifth, the clinical heterogeneity of the study population may increase variability in response and limit conclusions regarding specific diagnostic subgroups. At the same time, this heterogeneity reflects the population for whom the workshop is intended in routine practice. Sixth, because the intervention is delivered in successive workshop groups, participants attending the same workshop may show some residual within-group correlation despite individual randomization and standardized intervention delivery. This potential dependence will be addressed analytically using a partially nested mixed-effects structure. However, the limited number of workshop groups may reduce the precision with which the workshop-level variance component can be integrated.

Seventh, analyses of sex-related differences and interactions will be exploratory, as the trial was not specifically powered to assess effect modification by sex and an unequal sex distribution is expected in this population.

Finally, losses to follow-up may occur due to the duration of the workshop, the face-to-face attendance required for the sessions, and repeated questionnaire completion. To reduce this risk, standardized procedures for follow-up and contact with the participants will be applied.

## 4. Conclusions

This protocol describes a mixed-methods randomized controlled clinical trial with a qualitative strand designed to evaluate a multicomponent workshop based on NPhTs for people with chronic non-cancer pain. The study is designed to generate evidence on the effectiveness and to provide complementary information on the participants’ experiences, perceived usefulness, and acceptability-related aspects of a group-based intervention focused on therapeutic education, self-care, and continuity in the use of non-pharmacological strategies. Its findings may contribute to informing interdisciplinary care models, although the transferability of the intervention to other healthcare settings will require further evaluation in different organizational and clinical contexts.

## Figures and Tables

**Table 1 healthcare-14-03063-t001:** Planned outcomes and measurement instruments.

Outcome/Domain	Measurement Instrument or Indicator
Health-related QoL	EuroQol-5D (EQ-5D): index value and visual analogue scale [27]
Pain intensity	0–10 numeric pain rating scale [28]
Subjective well-being	0–10 numeric well-being scale developed within the program [22,23]
Self-esteem	Spanish version of the Rosenberg Self-Esteem Scale [29]
Resilience	Spanish version of the Brief Resilience Scale (BRS) [30,31]
Anxiety and depressive symptoms	Spanish version of the Hospital Anxiety and Depression Scale (HADS) [32]
Pain catastrophizing	Spanish version of the Pain Catastrophizing Scale (PCS) [33]
Mood	Ad hoc categorical item: cheerful, normal, discouraged, or depressed [22,23]
Medication use	Number of medications and changes in analgesic regimen [22,23]
Health habits	Ad hoc items on self-reported habit improvement [22,23]
Healthcare resource use	Number of emergency department visits and scheduled consultations related to CP or to exacerbation or complications of the underlying condition causing pain
Participant experience	Ad hoc questionnaires and semi-structured interviews

**Table 2 healthcare-14-03063-t002:** Participant timeline and study procedures.

Timepoint/Period	Timing	Participants Involved	Main Procedures
Screening/inclusion	Before baseline	Potentially eligible patients	Eligibility assessment; participant information; informed consent
T0: Baseline	Month 0	Both groups	Randomization; collection of sociodemographic and clinical variables; outcomes assessment (1)
Intervention period	Month 0–1	Intervention group	Workshop sessions
T1: End of workshop	Month 1	Both groups	Outcomes assessment (2)
		Intervention group	Workshop satisfaction and perceived impact
Qualitative follow-up	Month 2–3	Intervention group	In-depth semi-structured interviews (3)
T2: Follow-up	Month 4	Both groups	Outcomes assessment (2)
		Control group	Offer of the workshop
T3: Follow-up	Month 7	Intervention group	Outcomes maintenance assessment (2)

## Data Availability

No new data were created or analyzed in this study. Data sharing is not applicable to this article.

## Abbreviations

The following abbreviations are used in this manuscript:

ANOVA	Analysis of variance
BRS	Brief Resilience Scale
CONSORT	Consolidated Standards of Reporting Trials
COREQ	Consolidated Criteria for Reporting Qualitative Research
CP	Chronic pain
EQ-5D	EuroQol-5D
HADS	Hospital Anxiety and Depression Scale
IASP	International Association for the Study of Pain
MCID	Minimal clinically important difference
NPhT	Non-pharmacological therapy
NPhTs	Non-pharmacological therapies
PCS	Pain Catastrophizing Scale
QoL	Quality of life
RPM	Remote Patient Monitoring
SD	Standard deviation
SPIRIT	Standard Protocol Items: Recommendations for Interventional Trials
SRQR	Standards for Reporting Qualitative Research

## Appendix A

**Table A1 healthcare-14-03063-t0A1:** Workshop content and facilitators.

**Session 1:**
**Objectives:** To explore the participants’ expectations before the workshop; to understand what chronic pain is, how it develops, and how it differs from acute pain; to understand the relationship between physical and emotional pain; to identify limiting beliefs; and to learn the two techniques that participants will practice at home. **Content, techniques, facilitator, duration, and materials:** 1. Welcome and signing of participation and image-use consent forms. (Physician 1) 25 min. 2. Assessment of workshop expectations (brainstorming). (Physician 1) 20 min. 3. Presentation: Pathophysiological mechanisms of pain. Differences between acute and chronic pain. (T: ED) (Physician 2) 60 min. 4. Presentation: Influence of emotions on pain intensity. (T: ED) (Physician 1) 60 min. 5. Activity: My limiting beliefs. (T: TCC) (Physician 1) 15 min. 6. Activity: Mental analgesia technique. (T: meditation) (Physician 1) 15 min. 7. Homework assignments: The participants are instructed to perform the “mirror affirmations to motivate change” and “mental analgesia technique” activities every day and record them on a paper tracking sheet. (Physician 1) 15 min. 8. Materials provided: Description of the homework assignments and a tracking sheet; physical exercise guide (part 1).
**Session 2:**
**Objectives:** To review the homework assignments and provide guidance when necessary; to reinforce the mental analgesia technique; to recognize how chronic pain affects participants’ lives; to understand the grieving process; to learn techniques for forgiving others and for self-acceptance; to identify low self-esteem and strengthen it; and to increase hope that pain can be controlled and well-being improved. **Content, techniques, facilitator, duration, and materials:** 1. Sharing the results of homework assignments. (Physician 1) 20 min. 2. Activity: Repetition of the mental analgesia technique. (T: meditation) (Physician 1) 10 min. 3. Presentation: Pain and its impact on the patient’s life: “You are not your pain.” (T: TCC, TAC, PRT) (Psychologist) 60 min. 4. Activity: Limiting labels. (T: role play) (Physician 1 and 5 patients) 15 min. 5. Presentation: Self-esteem. What is it? Activities: Reading “When I Truly Loved Myself”; self-esteem mirror affirmation (tools to increase self-confidence). (T: TAE) (Physician 1) 15 min. 6. Activity: Self-healing meditation. (T: meditation) (Physician 1) 10 min. 7. Activity: Forgiveness and self-forgiveness. Examples from experience. (T: Ho’oponopono, TAC) (Physician 1) 10 min. 8. Presentation: Physical exercise as a tool to reduce pain. Activity: Performance of physical exercises. (T: EHS, EP) (Physiotherapist) 35 min. 9. Talk: Examples of individuals with personal improvement experiences (a real patient from a previous workshop shares their experience). (T: MC) (patient contributor) 20 min. 10. Activity: Motivation for change. Life purpose. (Video of a person overcoming major limitations). (T: MC) (Physician 1) 5 min. 11. Homework assignments: The participants are taught two new tasks (Ho’oponopono technique and self-healing meditation) to practice during the week and are instructed to continue performing the Session 1 activities daily. (Physician 1) 10 min. 12. Materials provided: Description of the homework assignments; physical exercise guide (part 2).
**Session 3:**
**Objectives:** To review the homework assignments and provide guidance when necessary; to recognize how daily habits influence chronic pain; to identify habits that can improve pain control (nutrition, physical exercise, and sleep); to reinforce forgiveness of others and oneself; and to motivate behavioral change. **Content, techniques, facilitator, duration, and materials:** 1. Sharing the results of homework assignments. (Physician 1) 20 min. 2. Presentation: How personal conflicts influence pain. (T: ED, video) (Physician 1) 25 min. 3. Presentation: Promotion of healthy habits: General approach. Activity: Self-assessment of habits. (T: EHS, video, MC) (Physician 1) 20 min. 4. Presentation: Healthy eating. (Nutritionist and Nurse) (T: EHS, MC) 40 min. 5. Presentation: Sleep quality. (Nurse) (T: EHS) 30 min. 6. Activity: Physical exercise through dancing. (T: EP) (Physician 1) 10 min. 7. Activity: Metta meditation (focused on forgiveness). (T: meditation) (Physician 1) 10 min 8. Activity: Connecting with one’s inner self. (T: Reading “Who You Are”, song “I Will Wake You Up”) (Physician 1) 15 min. 9. Activity: Motivation for change, “Awakening the Senses.” (T: song, mindfulness, MC) (Physician 1) 10 min. 10. Talk: Experience shared by a patient from a previous workshop. (T: MC) (patient contributor) 20 min. 11. Homework assignments: The participants are given new tasks to complete during the week: improve one or two habits; identify what they say to themselves when they make a mistake and change their internal dialogue; and practice Metta meditation. They are instructed to continue performing the Session 1 activities daily. (Physician 1) 10 min. 12. Materials provided: Description of the homework assignments; and information on nutrition and sleep quality.
**Session 4:**
**Objectives:** To review the homework assignments and provide guidance when necessary; to understand the need to participate actively in improving one’s own health; to learn how to prepare for a medical consultation; to reinforce tools and advice that reduce pain and improve health; to address questions about the disease and/or treatment; to learn how to use visualization to achieve goals and improve the current situation; and to motivate change. **Content, techniques, facilitator, duration, and materials:** 1. Sharing the results of homework assignments. (Physician 1) 20 min. 2. Presentation: Active participation in my own recovery. How to cope with illness. (T: ED, MC) (Physician 3) 90 min. 3. Presentation: Creative visualization. (T: MC) (Physician 1) 15 min. 4. Activity: Physical exercise through dancing. (T: EP) (Physician 1) 15 min. 5. Activity: How to improve self-esteem: Video “You Are Not Good Enough,” about well-known individuals who persisted in pursuing their goals despite initial failures and ultimately achieved them. (T: MC, video) (Physician 1) 5 min. 6. Activity: Brief verbal survey to assess patients’ current status (whether they are controlling their pain and their current mood). (Physician 1) 10 min. 7. Talk: Experience shared by a patient from a previous workshop. (T: MC) (patient contributor) 20 min. 8. Activity: Self-esteem meditation. (T: meditation) (Physician 1) 10 min. 9. Activity: Self-connection through music: “The Eternal Sun.” (T: mindfulness, MC) (Physician 1) 10 min. 10. Homework assignments: The participants are taught a new task for the week, “Creative visualization,” and are instructed to continue performing the Session 1 activities daily. (Physician 1) 15 min. 11. Materials provided: Description of the homework assignments.
**Session 5:**
**Objectives:** To review the homework assignments and provide guidance when necessary; to review the tools, advice, and therapies presented and practiced during the workshop; to address questions about the tools; to collect the tracking sheets completed at home; to evaluate outcomes using scales and questionnaires through the app; and to thank patients for their participation and work. **Content, techniques, facilitator, duration, and materials:** 1. Sharing the results of homework assignments. (Physician 1) 15 min. 2. Presentation and discussion: Review of the tools explained during the workshop. Group sharing. Question-and-answer session. (Physician 1) 60 min. 3. Collection of the tracking sheets completed by patients during the workshop and provision of the recommendations guide. (Physician 1) 15 min. 4. Talk: Experience shared by a patient from a previous workshop. (patient contributor) 20 min. 5. Activity: Workshop evaluation and completion of assessment scales. (patients, with guidance from facilitators) 40 min. 6. Activity: Physical exercise through dancing. (T: EP) (Physiotherapist) 20 min. 7. Talk: Information about the upcoming follow-up dates. (Physician 1) 10 min. 8. Activities: Thanking patients for their trust in the workshop and encouraging them to continue applying and further developing the tools to control pain and cope better with illness; final closing and farewell. (Physician 1) 30 min. 9. Materials provided: Guide containing the tools presented during the workshop and additional advice; information on chronic pain patient associations located in the hospital’s catchment area.

T: Technique used; ED: pain education; TCC: cognitive behavioral therapy; TAC: Acceptance and Commitment Therapy; PRT: Pain Reprocessing Therapy; TAE: exercises to identify and improve low self-esteem; Ho’oponopono: technique for working on forgiveness; MC: motivation for change; EHS: healthy lifestyle education; EP: physical exercise. Note: PowerPoint presentations containing the content of the talks are available. Each facilitator developed their own presentations, which will remain unchanged throughout this study to ensure intervention fidelity. In some sessions, printed supporting materials are also provided to patients, as indicated in the table at the end of each session.

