Adherence to the intervention will be monitored through session-attendance records. The participants attending at least four of the five workshop sessions will be classified as adherent for the per-protocol sensitivity analysis. Completion of the outcome assessments will be recorded separately and will not determine adherence status or inclusion in the intention-to-treat population. The participants who discontinue or attend fewer than four sessions will continue to be invited to complete the scheduled follow-up assessments unless they withdraw consent.

The intervention groups from the different workshop sessions will not communicate with one another and will not know each other. The participants in the control groups will not communicate in any way with the other study participants; they will only have contact with the research support technician who provides assistance with the app.

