#### 2.3.2. Participant Timeline

The participant timeline is summarized in Table 2. After eligibility assessment and written informed consent, the participants will complete the baseline assessment and will be randomly allocated to either the intervention group or the control group.

(1) Baseline assessment: All outcomes included in Table 1, except health habits and participant experience. (2) Follow-up assessments: All outcomes included in Table 1, except semi-structured interviews; only the ad hoc questionnaires (satisfaction questionnaire and self-assessment questionnaire on the impact of the workshop). (3) Qualitative study: Semi-structured interviews.

The participants in the intervention group will attend the five-session workshop over 1 month. They will complete follow-up assessments at the end of the workshop (1 month after baseline); 4 months after baseline (corresponding to 3 months after completion of the workshop); and 7 months after baseline (corresponding to 6 months after completion of the workshop).

The participants in the control group will complete assessments at baseline, 1 month after baseline, and 4 months after baseline. After completing the 4-month assessment, the participants in the control group will be offered the opportunity to attend the workshop.

Semi-structured interviews for the qualitative strand will be conducted after completion of the workshop, preferably between the first and second month after the intervention.

This study is expected to last 2 years. Recruitment will take place over 12 months, and follow-up will be completed 18 months after the start of this study. During the final 6 months, data cleaning, analysis, and dissemination will be conducted.

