#### 2.3.4. Data Management

The study data will be managed using the MoviSalud RPM (Remote Patient Monitoring) platform, adapted for this project. The platform will centralize data entered by the participants through the mobile app and will allow the research team to access these data through a professional web portal.

An internal medicine physician from the research team will conduct recruitment through a telephone interview to verify whether the patient meets the inclusion criteria. If eligible, the physician will inform the patient about this study and the possibility of being allocated to either the intervention or the control group and will obtain informed consent. Once a cohort of 40 patients has been recruited, the physician will notify the research support technician, who will register and enroll them in the app.

Once enrolled in the platform, the patient will have access exclusively to the baseline assessment forms prior to randomization. Once patients have completed the baseline assessment, randomization will be requested. Treatment allocation cannot be predicted in advance.

Allocation to the study arm will be performed automatically by the system through an atomic and irreversible transaction, with a timestamp and audit trail; no individual will be involved in the allocation process. The recruitment wave will then be closed, the corresponding workshop cohort will be established, and the control group will be activated. Within each combination of recruitment wave and stratum, permuted blocks of size 4 or 6 will be generated, with the block size selected randomly and independently for each block, with a probability of 0.50 for each size. With recruitment waves of approximately 40 participants divided into two sex strata, and considering the higher expected prevalence of women among individuals with chronic pain, the male stratum may comprise approximately 10–12 participants per wave. Blocks of size 8 would, therefore, result in a relatively high number of incomplete blocks at the end of each recruitment wave, which would be contrary to the intended purpose of blocking. Block sizes of 4 and 6 limit the maximum imbalance within each stratum to three participants, while preserving allocation unpredictability.

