### 2.5. Data Analysis

#### 2.5.1. Quantitative Analysis

Statistical analysis will be performed using IBM SPSS Statistics, version 27.0 (IBM Corp., Armonk, NY, USA). For categorical variables, absolute frequencies and percentages will be calculated. For quantitative variables, means and standard deviations (SDs) or medians and interquartile ranges will be reported, depending on whether the variables follow a normal distribution. This study has a single confirmatory primary analysis: the baseline-adjusted between-group difference in the EQ-5D index at 1 month, evaluated at a two-sided α level of 0.05. The EQ-5D contrast at 4 months and the prespecified secondary outcomes will be treated as supportive secondary analyses. Analyses of ad hoc outcomes, treatment-effect modification, subgroup analyses, per-protocol analyses, and the month-seven maintenance assessment will be considered exploratory. No global formal adjustment for multiplicity will be applied to these secondary and exploratory analyses because they will not be used to support independent confirmatory claims. Effect estimates and 95% confidence intervals will be emphasized; *p* values for secondary and exploratory analyses will be reported as nominal and interpreted cautiously in the context of multiple testing, and isolated nominal *p* values < 0.05 will not be considered confirmatory evidence.

Continuous secondary outcomes measured repeatedly will be analyzed using analogous linear mixed-effects models. Binary outcomes will be analyzed using logistic generalized linear mixed-effects models; count outcomes will be analyzed using Poisson or negative-binomial mixed-effects models, according to dispersion; and ordinal outcomes will be analyzed using an appropriate ordinal mixed-effects model when applicable.

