### 2.6. Rigor, Validity, and Reliability

The quantitative and qualitative strands of this study were designed and will be reported according to their respective standards: SPIRIT [42] and CONSORT [43] for the randomized trial, and SRQR [44] and COREQ [45] for the qualitative study based on semi-structured interviews. The intervention was described in accordance with the Template for Intervention Description and Replication (TIDieR) checklist [46], which is provided in Supplementary Materials.

The methodological quality of the quantitative strand will be ensured by the use of validated instruments to assess the main study variables. These include the EQ-5D for health-related QoL [27], the Numerical Rating Scale for pain intensity [28], the Rosenberg Self-Esteem Scale [29], the BRS for resilience [30,31], the HADS for anxiety and depression [32], and the PCS for pain catastrophizing [33]. Data collection will be standardized across the predefined assessment time points for both groups during the comparative period. In addition, the intervention will follow a homogeneous structure in terms of sessions and content, and adherence will be monitored through attendance records. To reduce the risk of bias in between-group comparisons, the researcher responsible for the quantitative data analysis will remain blinded to the participants’ allocation.

In the qualitative strand, rigor will be addressed according to Lincoln and Guba’s quality criteria, including credibility, transferability, dependability, and confirmability. Participants with different sociodemographic profiles will be included to capture a sufficient diversity of experiences and perceptions regarding the intervention. The analytical process, including decisions related to coding, categorization, and interpretation, will be documented in detail to enhance the traceability of the analysis and allow it to be reviewed.

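### The 1-month EQ-5D, the only confirmatory endpoint, is completed in one arm inside Session 5 with guidance from the unblinded workshop facilitators, and in the other arm outside any session without them

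*Protocol article*

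**What the plan says.** The single confirmatory analysis (Section 2.5.1) is "the baseline-adjusted between-group difference in the EQ-5D index at 1 month, evaluated at a two-sided α level of 0.05".

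**Intervention arm.** Section 2.3.2 says of these participants: "They will complete follow-up assessments at the end of the workshop (1 month after baseline"). Table 2 labels T1 as the end of the workshop, at month 1. In Appendix A, Table A1, one objective of Session 5 is "to evaluate outcomes using scales and questionnaires through the app", and item 5 of that session is "Activity: Workshop evaluation and completion of assessment scales. (patients, with guidance from facilitators) 40 min".

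**Control arm.** Section 2.3.2: "The participants in the control group will complete assessments at baseline, 1 month after baseline, and 4 months after baseline". Section 2.1.4 gives controls the platform only for questionnaires and records. Section 2.1.3 says of their contacts that "they will only have contact with the research support technician who provides assistance with the app".

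**Both arms.** Section 2.3.3 offers every participant reminders and help with the app by telephone, through a relative, or at an appointment in the hospital. Section 2.6 states: "Data collection will be standardized across the predefined assessment time points for both groups during the comparative period". Section 2.1.1 says that neither participants nor providers can be blinded; only the analyst is.

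**The concern.** The EQ-5D is self-rated by people who know their arm. In the intervention arm, the programme has them rate themselves in the group, at the closing session, guided by the people who have just delivered the treatment. Nothing comparable happens in the control arm. If patients answer more favourably in that setting, the shift enters one arm only and adds directly to the estimated effect. Adjusting for baseline does not remove it, because it arises at T1. Blinding the analyst does not remove it either, because it is already in the data.

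A second route is completeness. Session 5 attendees have 40 scheduled minutes for the scales, while controls and absentees depend on reminders and individual help. Missing T1 data could therefore differ by arm and by attendance.

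The Limitations section names lack of blinding, expectations, social desirability and group influence. It does not mention facilitator-guided completion in one arm, which, unlike the lack of blinding, can be avoided. The protocol takes this precaution elsewhere: Section 2.3.3 has the qualitative interviews done by researchers who do not deliver the workshop, so that participants can speak freely.

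**Working it through.** **1. Are the Session 5 scales the T1 outcome scales?** Table A1 does not name the EQ-5D. The link runs through three places:
- The Session 5 objective refers to evaluating outcomes through the app.
- Section 2.3.2 and Table 2 place T1 at the end of the workshop.
- The notes to the timeline in Section 2.3.2 make the Table 1 instruments due at follow-up assessments, and the EQ-5D index is among them.

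Reading item 5 as the T1 assessment is the natural reading.

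**2. Is it part of the session itself?** The timed items of Session 5 sum to 15 + 60 + 15 + 20 + 40 + 20 + 10 + 30 = 210 min = 3.5 h, the full session length. Completion is therefore built in. It follows 15 + 60 + 15 + 20 = 110 min of homework sharing, review of the tools, collection of tracking sheets and a former patient's testimony.

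**3. The arms side by side at T1**

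| | Intervention | Control |
|---|---|---|
| Medium | app | app |
| Setting | group, closing session | outside any session |
| Helper | workshop facilitators | research support technician |
| Help under Section 2.3.3 | available | available |
| Anchor | end of workshop, equated with 1 month | 1 month after baseline |

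**4. The plan's own figures.** A two-sided t-test with α = 0.05, power 0.80 and d = 0.50 needs 63.77, so 64 per arm and 128 in total. Then 128/0.80 = 160, and 0.50 × 0.197 = 0.0985, about 0.10. All agree with Section 2.2.1, and the present point changes none of them.

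**5. Illustration of scale.** The inputs are SD 0.197 and 64 per arm (Section 2.2.1). The shift b is assumed, with no true effect.
- SE = 0.197 × √(2/64) = 0.0348.
- P(reject) = 1 − Φ(1.960 − b/SE) + Φ(−1.960 − b/SE).
- b = 0.03: b/SE = 0.861, giving 0.136 + 0.002 = 13.8%.
- b = 0.05: b/SE = 1.436, giving 30.0%.
- b = 0.01 and 0.02 give 6.0% and 8.9%.
- With an assumed baseline–T1 correlation of 0.5, SE falls to 0.0348 × √0.75 = 0.0302. The four shifts 0.01, 0.02, 0.03 and 0.05 then give 6.3%, 10.2%, 16.9% and 38.1%.

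**6. Timing (secondary).** Five weekly sessions put Session 5 at 4 × 7 = 28 days after Session 1. Baseline comes earlier still: "Once patients have completed the baseline assessment, randomization will be requested" (Section 2.3.4), and the workshop cohort is formed after that. The lag from baseline to Session 1 is not stated. For assumed lags of 0, 7 and 14 days, Session 5 falls on day 28, 35 and 42 after baseline, against about day 30 for controls.

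**The case against.** **Controls are not left alone.** A reader might infer that one arm is guided and the other is not. Section 2.3.3 rules that out, because technical help is open to all. What remains is a difference in helper and setting.

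**A different clock is not stated.** A reader might conclude that the arms are measured at different times. Section 2.3.2 and Table 2 put both nominally at month 1. Any gap depends on an unstated lag, and visit windows are often left to the full protocol. What stands is that the two anchors agree only if Session 1 starts close to baseline.

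**No flat contradiction.** Instruments, app and nominal time points are the same in both arms, and Section 2.6 does not promise the same helper or room. It is fair to call this a tension that needs reconciling.

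**Guidance may be technical.** Table A1 does not say that facilitators see or influence answers, and the item also covers the workshop evaluation. This is true, and it is why neither the size nor the direction of a bias is established. But nothing limits the guidance to technical matters, and the group setting remains in any case.

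**Some bias would survive the change.** Participants will know their arm wherever they answer, and the Limitations section says so. Only the increment from in-session completion is at issue.

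**Missing data are partly handled.** Non-adherent participants stay invited, and the multiple-imputation sensitivity analysis uses attendance. This addresses missingness under its assumption; it does not address how observed answers were obtained.

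**Conclusion.** The point holds as an avoidable difference between the arms in how the primary outcome is collected. At T1 the intervention arm answers inside the workshop with guidance from unblinded facilitators, and the control arm does not. The safeguards that the protocol offers do not reach this.

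The documents give no measure of the bias. The rejection rates of about 14% and 30% follow from assumed shifts of 0.03 and 0.05. The first is the low end of the clinical-relevance range in Section 2.3.1, which says nothing about response style. They show how sensitive the test is to such a shift, and a reader should not take them as the trial's expected false-positive rate.

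The differing anchors are a lesser matter to clarify. The conclusion rests on reading the Session 5 scales as the T1 assessment, which Section 2.3.2 and Table 2 support.

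**What to change.** - Keep only the satisfaction and workshop evaluation in Session 5.
- Have both arms complete the T1 outcome scales on the app outside the workshop, in one common calendar window per recruitment wave (for example, the 7 days after that wave's Session 5).
- Limit help at T1 to staff who do not deliver the workshop, that is, the research support technician.
- Anchor T1 and T2 to the same date in both arms of a wave.
- Reconcile Section 2.3.2, Section 2.6, Table 2 and Session 5 of Table A1 accordingly.

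The cost is protocol wording and app reminder dates; the sample-size calculation stays at 128 and 160. T1 completion among attendees may fall slightly. Existing reminders help, and the recruitment target of 180 in Section 2.2.1 leaves some room: 128 evaluable participants would still be reached with 1 − 128/180 = 28.9% loss. The 20% allowance itself should not be claimed to cover the change. It comes from previous workshop experience and may already reflect in-session completion.
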